## Abstract

Background: Although undergoing an abortion is stressful for most women, little attention has been given to their psychological wellbeing. This protocol aims to assess the feasibility, acceptability, and primary effects of a complex intervention to promote positive coping behaviors and alleviate depression symptoms among Chinese women who have undergone an abortion. Methods: A two-arm randomized controlled trial design will be used. Participants will be recruited at their first appointment with the abortion clinic and randomly allocated to receive either the Stress-And-Coping suppoRT (START) intervention (in addition to standard abortion care) or standard care only. All participants will be followed-up at two- and six-weeks post-abortion. Approval has been granted by local and university ethics committees. This research was supported by an Australian Government Research Training Program Scholarship. Discussion: The results will assist refinement and further evaluations of the START intervention, contribute to improved abortion care practices in China, and enrich the evidence on improving women’s psychological well-being following abortion in China. Trial registration: Registered at the Chinese Clinical Trials.gov: ChiCTR2100046101. Date of registration: 4 May 2021.

## 1. Introduction

Induced abortion is common around the world. In 2015–2019, a third of all pregnancies ended in abortion (approximately 77.3 million abortions each year) [1]. Accessing good-quality abortion care is a fundamental human right, an important component of sexual and reproductive health services, and an essential way to achieve global health commitments [2] such as the Sustainable Development Goals (SDGs) [3]. Generally, abortion is physically safe when conducted using WHO-recommended methods by appropriately trained professionals [4]. For most women, the main challenge when choosing a first-trimester abortion is their emotional and psychological wellbeing [5]. Some women cope well with abortion and do not experience negative psychological consequences [6,7]. Some might even find positive meaning and embrace healthy behaviours after an abortion [8,9], whereas some report ongoing distress and mental health issues [5,10].

The Transactional Model of Stress and Coping helps to explain the psychological variability of abortion [10,11]. According to this model, abortion is a dynamic stressful life event that happens in response to an unwanted/unintended pregnancy. In this circumstance, a woman first appraises the significance/severity of the pregnancy and then evaluates her options and coping resources at her disposal [10,12]. A woman’s appraisal mediates her coping behaviours and the psychological consequences of an abortion (see Figure 1) [12]. The Transactional Model of Stress and Coping suggests that by offering women the support they need, they can adjust their coping processes and achieving positive health outcomes.

Despite the critical role of support to women accessing abortion, little attention has been paid to the psychosocial aspects of care [13]. A recently published systematic review found that in the past ten years, only ten experimental studies had been conducted to address the psychological needs of women undergoing abortion [14]. All interventions used a single-component design (e.g., music therapy, information support, or implementation of mandated waiting or counselling policies), and none were informed by a theoretical framework. Conflicting outcomes and methodological limitations hindered conclusions about which intervention could reasonably be adopted to improve women’s psychological well-being [14].

Abortion occurs in a socio-cultural context, and local policies regarding abortion accessibility play an important role in women’s psychological response toward an abortion. As the most populous country in the world, about 10 million abortions were conducted in China in 2019 [15]. China has one of the most liberal abortion policies amongst Asian countries, which allows first-trimester abortion without restriction, except for the prohibition of sex-selective abortions. Abortion is also socially acceptable in China, and most abortions that occur in China are due to unwanted pregnancies consistent with a societal desire for small families and timed birth. A recent study revealed that around a quarter of women seeking an abortion in China experienced high stress and moderate-to-severe depression [16]. Chinese women’s unmet support needs when seeking abortion were predictive of adverse psychological outcomes.

In the absence of available evidence, our research team developed the STress-And-coping suppoRT intervention (START). Underpinned by the Transactional Model of Stress and Coping, the START intervention will provide women with information, coping skills, and support to achieve positive short- and long-term health. The intervention is innovative and based on (1) current available evidence, (2) a sound understanding of the target population, (3) informed by Medical Research Council (MRC) guidance for complex interventions [17], (4) the Intervention Mapping (IM) framework [18], and (5) a five-step iterative pathway to gradually shape the intervention design [19].

The aim of this trail is to assess the START intervention among Chinese women undergoing an abortion. Its specific objectives are to:Determine the feasibility of the START intervention according to eligibility, recruitment, intervention delivery, and retention data;Evaluate the acceptability of the START intervention among participants based on the Theoretical Framework of Acceptability (TFA) of Health Care Interventions;Test the preliminary efficacy of the START intervention on women’s depression symptoms, coping behaviors, self-efficacy, perceived support levels, intimate relationship satisfaction, post-abortion personal growth, and abortion relevant outcomes compared with women receiving standard abortion care.

## 2. Materials and Methods

The study adopts a two-arm randomized controlled trial design with quantitative and qualitative information collected. Participants will be randomly allocated to receive either the START intervention in addition to standard abortion care or standard abortion care only with a 1:1 allocation rate. The study design is directed by the CONSORT statement and its extensions [20,21] and the Standard Protocol Items: Recommendations for Interventional Trials (SPIRIT) 2013 guideline for protocols of randomized trials [22]. The research activities inconsistent with the real-world clinical practice are outlined in Figure 2.

### 2.1. Setting

This study will be conducted in the Family Planning and Reproductive Health Centre (FPRHC) of a tertiary hospital in Beijing, China. Participants will be recruited from the outpatient unit of the FPRHC, where abortion-related services are normally provided.

### 2.2. Participants

Women will be invited to participate in the study if they meet the following criteria: (1) Chinese citizens or living in China; (2) can speak, read, and write in Chinese; (3) are 18 years or older; (4) seeking termination of an intrauterine pregnancy for non-medical reasons; (5) less than 14 gestational weeks; (6) certain about their abortion decision and indicate the decision is of their free will; and (7) own a smartphone. Women will be excluded if they: (1) are presenting to FPRHC for post-abortion follow-up examination or secondary treatment of an incomplete abortion); (2) require an abortion for medical reasons; (3) are currently receiving mental or psychological treatment; or (4) unable to give informed consent (e.g., severe intellectual disability).

### 2.3. Interventions

A psychologist as well as clinic staff who provide direct care will be responsible for maintaining the quality of care and women’s safety. See Table 1 for a detailed description of the START intervention and standard abortion care according to the template for intervention description and replication (TIDieR) [23]. Generally, the START intervention involves three interacting components: (1) a 30-minute face-to-face consultation immediately after a woman’s enrolment; (2) information support including a printed booklet and an online information platform available to them from the consultation until closure of the project; and (3) timely communication channels with health providers (a hotline staffed between the hours of 8 a.m. to 5 p.m. and a WeChat-based public profile page) valid until 6 weeks post-abortion. Table 2 presents the specific content of the information booklet and platform.

### 2.4. Outcomes

#### 2.4.1. Feasibility Outcomes

Feasibility outcomes include eligibility and intervention delivery data, which will be collect by a research logbook and participants’ completion of questionnaires. The specific outcomes are:Proportion of women who meet the eligibility criteriaProportion of eligible women who are recruitedProportion of recruited women who receive the allocated intervention to which they are randomizedWithdrawal or loss to follow-up rateMissing data rate

#### 2.4.2. Acceptability Outcomes

Acceptability refers to retrospective acceptability assessed after participating in the intervention. Phone calls will be made to all participants in the intervention group at the last follow-up. A questionnaire based on the TFA framework of Health Care Intervention [24] will guide the recorded phone interview. The questionnaire will include both closed- and open-ended questions representing all seven constructs of intervention acceptability: affective attitude, burden, perceived effectiveness, ethicality, intervention coherence, opportunity costs, and self-efficacy. Responses on closed-ended questions are on a Likert Scale from 1 to 5, and response labels vary depending on the item. For example, ‘to what extent was the intervention useful to you?’ has response options of 1 ‘not at all useful’ to 5 ‘extremely useful’. Responses to opened-ended questions will be noted and recorded. Examples of open-ended questions are ‘how do you feel about the intervention’, ‘which component of the intervention was most/least useful and why?’, and ‘did you encounter any barriers when participating in the intervention?’.

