### 2.8. Data Collection

Data collection will occur at five timeframes: T-0, during recruitment before randomization; T-1, on abortion day before discharge (normally 2 h post-abortion procedure); T-2, during women’s post-abortion exam visit, normally 2 weeks post-abortion; T-3, 6 weeks post-abortion; and T-4, post completion of all follow-ups of all participants. See Table 3 for detailed information on data collection, including What, Who, When, Where, How, and by What data.

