### 2.9. Data Analysis

Participant characteristics, feasibility outcomes, and quantitative acceptability outcome data will be summarized with descriptive statistics, including frequency counts and percentages (categorical variables) and mean with 95% confidence intervals (CIs) or standard deviation (continuous variables). Intervention feasibility and acceptability will be assessed against the following criteria: eligibility: ≥60% of patients screened will be eligible; recruitment: ≥80% of eligible participants will agree to participate; protocol fidelity: ≥90% of patients randomized to each group will receive the allocated intervention; retention: <20% of patients will be lost at 6 weeks after abortion; and missing data: <20% of data will be missing. Between-group differences of participant characteristics, baseline data, and effectiveness outcomes will be detected using Statistical Package for the Social Sciences (SPSS)^®^ version 23 [41]. Specifically, Chi square tests will be used for categorical/dichotomous variables, and *t*-tests or Mann–Whitney U tests for continuous variables (depending on normality). To capture changes in the effect outcomes over time, a general linear regression analysis will be performed. See Table 3 for the specific analysis approaches.

For qualitative data, audiotapes of telephone interviews will be transcribed and de-identified by the primary researcher. Transcripts and notes will be analyzed using the deductive approach of content analysis [42]. First, a structured analysis matrix will be developed based on the aims of the study and the TFA of Health Care Intervention. Then the primary researcher and nurse coordinator will independently review all de-identified data, and content fit the matrix. They will work together to group similar content within the matrix boundaries as categories, and then main categories. After abstraction of each category, the primary researcher and nurse coordinator will make a joint decision on how to model and report the results. Any discrepancies along the process will be discussed with a third reviewer until an agreement is reached. To preserve the original meaning of women’s statements, the data analysis process will be conducted using Chinese. Development of the analysis matrix and reporting process will use Chinese and English to reduce potential bias and build a shared vision among the research team.

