**Figure 2 ijerph-19-06611-f002:**
[figure not shown]
SPIRIT standard flow diagram.

**Table 1 ijerph-19-06611-t001:** Intervention description according to TIDieR checklist.

TIDieR Item	Intervention Group	Control Group
**1.** **BRIEF NAME**	The START intervention	Standard abortion care
**2.** **WHY**	Based on the Transactional Model of Stress and Coping, the START intervention intends to help women cope with abortion experience by addressing the specific stressors they face in the Chinese context, hence promoting well-being	N/A
**3.** **WHAT-Materials**	Consultation, an information booklet, a WeChat-based public profile page, and a hotline	N/A
**4.** **WHAT-Procedure**	All participants allocated to the intervention group will be offered a 30-min face-to-face consultation. The consultation includes a brief introduction of the public profile page, Q&A, and offering emotional support and information on available coping resources. A printed information booklet will be provided during the consultation. Meanwhile, by scan the QR code, participants will be endowed with unlimited access to the public profile page till the closure of the project. A hotline will also be offered.	(1) prior abortion consultation on informed choice of pregnancy; (2) abortion preparation education on abortion practice, and steps involved; (3) a brief discharge education session on warning signs of potential complications and post-abortion contraception; and (4) a regular 2-week post-abortion appointment to determine the completion of the abortion.
**5.** **WHO PROVIDED**	The consultation, information booklet, and managing the public profile page will be carry out by the primary researcher who is a qualified abortion counsellor. Hotline will be answered by a registered nurse who has more than 10 years clinical experience in abortion care.	Prior abortion consultation and post-abortion exam-by doctors Abortion preparation and discharge education-by nurses
**6.** **HOW**	Consultation (face to face) Information booklet (hard copy) Public profile page (internet) Hotline (telephone)	Face to face
**7.** **WHERE**	Consultation (the consultation room) Information booklet (the consultation room) Public profile page (WeChat based) Hotline (telephone-base)	Health centre facilities

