**Acceptability outcomes**				
Acceptability	T-3	Primary researcher; at clinic facilities, telephone-interview	Self-design questionnaire including closed-ended and open-ended questions	**Quantitative data** Descriptive statistics Chi Square test comparing differences between groups of categorical variables **Qualitative data** A deductive approach of content analysis

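### At 6 weeks women rate START aloud, on a recording, to the person who delivered most of it, so the acceptability result (objective 2) is at risk of upward social-desirability bias

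*Protocol article*

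**What the plan says.** Section 2.4.2 defines acceptability as a retrospective judgement made after taking part, collected in the intervention arm only: "Phone calls will be made to all participants in the intervention group at the last follow-up". The call is recorded and guided by a questionnaire with closed items scored 1 to 5 and open questions, covering seven constructs. The example of a closed item is "to what extent was the intervention useful to you?’ has response options of 1 ‘not at all useful’ to 5 ‘extremely useful".

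Section 2.8 sets the last follow-up of participants at "T-3, 6 weeks post-abortion". For acceptability, Table 3 gives the method as "Primary researcher; at clinic facilities, telephone-interview".

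Table 1, item 5, says who provides START: "The consultation, information booklet, and managing the public profile page will be carry out by the primary researcher who is a qualified abortion counsellor". The hotline is the exception; an experienced registered nurse answers it.

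Section 2.9 adds that "audiotapes of telephone interviews will be transcribed and de-identified by the primary researcher". The primary researcher and the nurse coordinator then review the de-identified data independently, and a third reviewer is consulted on discrepancies.

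**The concern.** Acceptability is one of the trial's three objectives, and the Conclusions section says the results will be used to refine START and direct a fully powered trial. A rating of usefulness, burden or ethicality is sensitive to who asks for it. Here the person asking has counselled the woman at a difficult time, runs the online page she may have used, and is recording her answer. Courtesy, gratitude or reluctance to criticise would all push the answer upwards.

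The planned quantitative analysis is essentially a descriptive summary of the answers. It has no means of separating a good intervention from polite respondents. Nor is this something an analysis plan could repair: who asks, and by what route, is fixed in Section 2.4.2 and Table 3.

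**Working it through.** **Who does what.** Setting the places side by side:

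- START consultation, booklet, profile page: primary researcher (Table 1, item 5).
- START hotline: a registered nurse (Table 1, item 5).
- T-3 acceptability call: primary researcher (Table 3).
- Transcription and de-identification: primary researcher (Section 2.9).
- Coding: primary researcher and nurse coordinator independently, with a third reviewer for discrepancies (Section 2.9).

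Three of the four START elements and the acceptability interview are in the same hands. The only independent input comes at coding, after the answers have been given.

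**Is the overlap unavoidable?** Section 2.7 says data collectors cannot be blinded. That explains why an interviewer would know the allocation. It does not require the interviewer to be the provider. Table 3 already has the nurse coordinator collecting data at T-1 and T-2, Section 2.2 requires every participant to own a smartphone, and Section 2.10 already leaves paper questionnaires with women to complete alone. The means of separating the two roles are in the plan.

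**How many START women may not be heard.** The plan's own recruitment figures come first:

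- Planned: 72 / (1 − 0.20) = 90, or 45 per arm, as stated in Section 2.5.
- Contingency: 72 / (1 − 0.35) = 110.8, against the stated 110 in Section 2.10, or 55 per arm.

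With the same attrition applied to the START arm:

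- 45 × 0.80 = 36 interviewed; 45 − 36 = 9 not heard.
- 55 × 0.65 = 35.75, about 36 interviewed; 55 − 36 = 19 not heard.

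**What the missing women could do to a result.** The documents give no expected rating, so this is an illustration only. Suppose 32 of 36 interviewed women (89%) are favourable:

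- 9 of 45 missing: from 32/45 = 71% to (32 + 9)/45 = 91%.
- 19 of 55 missing: from 32/55 = 58% to (32 + 19)/55 = 93%.

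Both ranges contain 89%, and both upper limits lie above it. They show how uncertain the figure for the whole arm would be. They do not show in which direction the interviewed women differ.

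**Size of the interviewer effect.** The documents contain nothing from which to calculate it.

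**The case against.** The plan has safeguards. The open questions ask for the least useful component and for barriers, so criticism is invited. The nurse coordinator codes independently. Withdrawal, loss to follow-up and missing data are feasibility outcomes in their own right (Section 2.4.1), with a criterion in Section 2.9, "retention: <20% of patients will be lost at 6 weeks after abortion", so the number of women lost will be visible. The criteria listed in Section 2.9 include no numerical threshold for acceptability, so no stated decision rule would flip. All of this stands and limits the seriousness of the point. None of it changes who is on the line when the woman answers, and later coding cannot undo restraint during the call.

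A reader might go further and infer that acceptability will be reported by the most favourable women, because those who dislike START leave before 6 weeks and are never asked. The documents do not support that. Section 2.4.2 plans calls to every START participant; any restriction to women who can be reached would follow from attrition and is not a stated rule. The article is silent on exit interviews, which the full protocol may cover. The challenges to completion that the Discussion names are the emotional period, the sensitive topic and the pandemic, not dissatisfaction with START.

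A reader might also want acceptability moved to 2 weeks, or the last available rating used. That would mix ratings given after different amounts of exposure. Section 2.4.2 wants a retrospective judgement, and Section 2.3 keeps the communication channels open until 6 weeks.

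**Conclusion.** The point holds for the interviewer. The main provider of START also collects the acceptability ratings, by voice and on a recording, and this exposes objective 2 to upward social-desirability bias. The direction rests on the general expectation that people soften criticism when speaking to the person concerned. The documents do not give the size, and none is claimed here.

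For attrition, the supported statement is narrower: about 9 of 45 START women at 20% loss, and about 19 of 55 at 35%, may not be heard, and the report should say so. These counts assume that loss in the START arm equals the overall planned rate. Nothing in the documents shows that the women not heard are less favourable. This is an inexpensive improvement to a data-collection rule and does not invalidate the objective.

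**What to change.** - Keep T-3 as the acceptability time point.
- Have the closed items self-completed at T-3, by smartphone link or form, without the provider present or on the line.
- Have the open-ended call made by an existing team member who did not deliver START. The nurse coordinator is the obvious candidate, provided that person is not the hotline nurse; the article does not say, so the sponsor should confirm it.
- Offer the same short closed form to women who withdraw earlier, and report those answers as given at withdrawal.
- Report acceptability with the number of randomised START women and the number not heard, without asserting how the latter would have answered.
- Amend Section 2.4.2 and the acceptability row of Table 3 to match.

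The cost is a short form, a reminder for those not returned, and a swap of tasks between existing staff. Some self-completed forms may still be missing; Section 2.10 itself treats interviewing as a way to reduce missing data. If the nurse coordinator makes the calls, both planned coders will have either delivered START or conducted the interviews, so the third reviewer's role becomes more important. The reported acceptability may be less favourable than under the present plan.
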